- 3) To investigate sensitivity of the  $VO_{2peak}$  test function to reflect actual changes in the maximal oxygen consumption. We hypothesize that a three-month IWT intervention will improve the maximal oxygen consumption and the improvement will be reflected in the  $VO_{2peak}$  test.

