detect the sensibility in changes in  $VO_{2peak}$ . Throughout the study period all participants will use the InterWalk application to engage in interval walking training (exposure) [6]. To assess convergent validity and to confirm diabetes status an OGTT is employed. Study participants will complete a variety of tests across three laboratory days, over a period of three months. Table 1 describes the sequence of the tests included in the study. The study timeline is depicted in Figure 1. Participants will be instructed to fast, refrain from smoking and physical activity for 9 hours prior to the tests. After the assessment or REE or the OGTT the participants will be offered a meal.

[figure not shown]

Figure 1: Study timeline

| Table 1 Measurements included in the study                        |                                                       |                           |
|-------------------------------------------------------------------|-------------------------------------------------------|---------------------------|
| Day 1                                                             | Day 2                                                 | Day 3                     |
| Medical examination                                               | REE                                                   | As day 2                  |
| Assessment of resting energy expenditure (REE)                    | 2-hour Oral glucose tolerance test (OGTT)             | A graded $VO_{2max}$ test |
| Anthropometric measures                                           | DXA scan                                              |                           |
| Self-administered free living smart-phone based $VO_{2peak}$ test | Self-administered Smart-phone based $VO_{2peak}$ test |                           |
| Paced free-living smart-phone based $VO_{2peak}$ test             | Paced smart-phone based $VO_{2peak}$ test             |                           |
| Assessment of walking-economy                                     | Assessment of walking-economy                         |                           |
| A graded $VO_{2max}$ test                                         |                                                       |                           |

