## METHODS

**Interval walking training:** After day 1 the participants will engage in a three-month interval walking training program. An Interval-walking bout will consist of repeated cycles of 3 minutes of fast and 3 minutes of slow walking at 70% and 40% of the smart-phone assessed peak  $\text{VO}_2$ -rate, respectively. IWT is conducted for at least 60 minutes per day, three days per week. Compliance is monitored continuously using the on-board accelerometer logger.

**Estimation of  $\text{VO}_{2\max}$ :**  $\text{VO}_{2\max}$  will be assessed by employing a graded walking test protocol on a treadmill (Technogym Runrace, Gambettola, Italy). The test consists of a 5-min warm-up (individually determined moderate walking pace, 0% incline) followed by 2-min stages of increasing inclines (2% per stage) at individually determined brisk walking pace until the following criteria were met: plateauing of heart rate and  $\text{VO}_2$  with incremental workloads, respiratory exchange ratio  $> 1.1$  [6]. Oxygen consumption will be assessed using continuous indirect calorimetric measurements (CPET, Cosmed, Italy) and heart rate monitoring (Polar Electro, Holte, DK).

**Walking Economy:** To assess economy during fast walking, the steady-state oxygen consumption will be estimated during steady-state walking at a fixed speed on a treadmill. (Technogym Runrace, Gambettola, Italy). Measurements are made after a 15 minute customization period at 3 km/h. After the end of the period, measurements also are made over 5 minutes at the participants fastest self-selected pace to provide additional time for patients to reach steady-state oxygen consumption. The mean oxygen consumption of the later 2 minutes will be used. Oxygen consumption will be assessed using continuous indirect calorimetric measurements (CPET, Cosmed, Italy) and heart rate monitoring (Polar Electro, Holte, DK). The test will be performed at the same speed at all test days.

**Demographic Information:** Height, weight, waist and hip circumference will be measured by standard procedures. Dual x-ray absorptiometry (iDXA; Lunar, Madison, WI) will be used to assess whole body adiposity.

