**Smart-phone administered  $\text{VO}_{2\text{peak}}$  test:** The test consists of four stages; 1) 30 seconds of standing still, 2) 2 minutes of slow walking, 3) 2 minutes of moderate walking at moderate intensity, 4) 2 minutes of walking at high intensity. The three later paces are self-selected. It is recommended that the phone is placed at the hips. However, it is likely that the phone might be placed at other body locations. Therefore the participant will be fitted with three phones; 1) at the hip, 2) hand-held and 3) on their upper-arm. Throughout the tests oxygen consumption will be monitored using continuous indirect calorimetric measurements (CPET, Cosmed, Italy) and heart rate monitoring (Polar Electro, Holte, DK). The test will be conducted as both a self-administered test and where the participants are paced during walking. To ensure test-retest reliability of the self-administered test, the participants perform two additional tests at home with two and four days apart from the second test day.

**Glucose Tolerance:** Following an overnight fast, an antecubital intravenous (i.v.) line will be placed and fasting plasma glucose, insulin, C-peptide, lipids, cytokines, and HbA1c will be determined. A standard 75 g oral glucose tolerance test (OGTT) will be performed over 2 hours with blood draws every 30 min for the measurement of glucose, insulin, and C-peptide.

**Resting Energy Expenditure (REE):** REE will be assessed via indirect calorimetry (Quark B2, Cosmed, Italy). REE will be assessed using a ventilated hood as described earlier [11].

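### One 9-hour limit covers both fasting and exercise, so recovery time since the last training session is not held equal between Day 1 and the later laboratory days

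*Protocol*

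**What the plan says.** The pre-test instruction is in the Protocol, STUDY DESIGN, under the study design paragraph: "Participants will be instructed to fast, refrain from smoking and physical activity for 9 hours prior to the tests". The same interval serves fasting, smoking and exercise, and no laboratory day is singled out. It is the only restriction on activity before testing in the text available.

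The exposure is described under METHODS, Interval walking training: "After day 1 the participants will engage in a three-month interval walking training program", with the dose given as "IWT is conducted for at least 60 minutes per day, three days per week". STUDY DESIGN adds that all participants train with the app for the whole study period. No time of day is fixed for sessions, and nothing separates them from laboratory days.

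On the visits: "Study participants will complete a variety of tests across three laboratory days, over a period of three months". Table 1 places the measurements as follows:

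- Resting energy expenditure, the smart-phone tests and walking economy: Days 1, 2 and 3.
- Graded VO2max test: Days 1 and 3.
- Oral glucose tolerance test and DXA: Days 2 and 3 only.

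Aim 2 (BACKGROUND) expects acclimatisation to improve walking economy and raise walking pace with fitness unchanged. Aim 3 concerns the change over the programme: "We hypothesize that a three-month IWT intervention will improve the maximal oxygen consumption".

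**The concern.** Nine hours is an overnight-fast interval. Applied to exercise, it does not keep the tests clear of the study's own exposure. Before Day 1 there is no programme session to recover from. Before Days 2 and 3 there may be one, at an interval that varies from patient to patient.

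The measures used for aims 2 and 3 are oxygen cost at a fixed speed, self-selected pace and a maximal-effort test. By restricting activity before testing at all, the Protocol accepts that recent activity can disturb them. If some effect of a session outlasts the 9 hours, it falls on only one side of a before/after comparison. Every participant trains, including the control group in Additional Protocol 2, so no untrained group would let such an effect cancel. At stake is how cleanly a change between Day 1 and a later day can be attributed to acclimatisation or training.

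**Working it through.** The only figure the plan states on this point is the 9-hour interval. No sample-size or power figure depends on it, so the check is a reading of the schedule plus clock arithmetic.

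**1. Is an evening session permitted?**
The laboratory start time is not given; assume 07:00 to 10:00.
Latest permitted activity = start time − 9 h.

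- 07:00 − 9 h = 22:00 the night before.
- 10:00 − 9 h = 01:00 the same night.

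A 60-minute session finishing by 22:00 is allowed at either end of the range.

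**2. On which days can it happen?**

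| | Day 1 | Day 2 | Day 3 |
|---|---|---|---|
| Programme session possible the evening before | No | Yes | Yes |
| Patient's own exercise possible the evening before | Yes | Yes | Yes |
| Walking economy and smart-phone tests | Yes | Yes | Yes |
| Graded VO2max | Yes | No | Yes |
| Glucose tolerance test | No | Yes | Yes |

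The imbalance applies to measures taken on Day 1 and again later. It does not apply to the glucose tolerance test, because both of its occasions fall after training has begun.

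**3. How many patients could be affected?**
Assume three sessions on separate days each week, placed without regard to laboratory days.

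- Chance of a session on the previous calendar day = 3/7 = 43%, or 50 × 3/7 ≈ 21 of 50 patients if all adhere.
- With two sessions a week, 2/7 = 29%; with four, 4/7 = 57%.
- Programme sessions before Day 1: 0%.

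This counts a session at any hour of the previous day, including one about 24 hours before testing. For late sessions only, assume an 08:00 start and session end times spread evenly over 07:00–23:00 (16 h). Ending less than 12 h before the visit but outside the 9-hour ban means ending between 20:00 and 23:00 (3 h):

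- 3/16 × 3/7 = 0.080, about 8%.

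Both figures are shares of patients exposed. Neither is an estimate of bias.

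**4. How long is the gap before the walking tests?**
Take the 9 hours to run to the start of testing, and the order in Table 1. On Days 2 and 3 the 2-hour glucose tolerance test precedes the walking tests.

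- Before the smart-phone tests: at least 9 + 2 = 11 h.
- One smart-phone test: 0.5 + 2 + 2 + 2 = 6.5 min; two tests: 13 min.
- Walking economy: 15 + 5 = 20 min.
- Before the Day 3 VO2max test: 11 h + 13 min + 20 min = 11 h 33 min at least.

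Resting energy expenditure, DXA and the meal add time that the Protocol does not specify.

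**5. Size of the after-effect.**
The Protocol gives no figure for the effect of a session on pace, economy or VO2max 9 or more hours later. Neither size nor direction can be computed from it.

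**The case against.** The case for leaving the rule alone is substantial. The 9-hour limit is stated clearly and nothing contradicts it. In Table 1's order, the walking tests on Days 2 and 3 come at least about 11 hours after the cut-off. No source in the Protocol shows that a walking session still matters by then. Residual fatigue would work against the improvement hypothesised in aim 3. The smart-phone test and VO2max share a laboratory day on Days 1 and 3, so a common residual state would touch both. Agreement within a smart-phone test is better protected still: "Throughout the tests oxygen consumption will be monitored using continuous indirect calorimetric measurements". The app log already holds the training times. Figure 1 and the participant information are not available here, and a spacing instruction may be given there.

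Most of this stands and limits the point. It does not remove it: same-day testing protects the comparison of changes only if the residual state shifts both measures alike, which the Protocol does not show. The log can date programme sessions, but it does not make recovery times equal, and the Protocol does not ask for it to be used this way.

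Four stronger readings are tempting, and the Protocol does not support them:

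- A reader might infer that after-effects *are* mixed with the training change. Late sessions are permitted, not scheduled, so the text supports only that they could be.
- A reader might infer that an acute exercise effect will pass for a training adaptation in the glucose tolerance test relative to baseline. Table 1 has no Day 1 glucose tolerance test. What remains is variable time since exercise on both of its days.
- A reader might take 43% as the share tested shortly after training. It is the share with any session on the previous day.
- A reader might expect the support-versus-control comparison to be distorted. Its outcome is adherence taken from the exercise log, which rest before testing does not bias.

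**Conclusion.** The point holds as a weakness in measurement standardisation. The Protocol does not hold time since the last session equal between Day 1 and the later days for walking economy, self-selected pace and VO2max, so residual effects could be mixed with the changes that aims 2 and 3 interpret. It is neither a contradiction nor a numerical error, and no bias can be quantified.

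The exposure is at most about 43% of adherent patients with a session on the previous day, and about 8% with a late-evening one under the end-time assumption above. Both figures assume that sessions are placed independently of laboratory days. The Day 1 contrast concerns programme sessions only. BACKGROUND describes these patients as having little training experience, which makes their own strenuous exercise before Day 1 less likely but does not exclude it. The conclusion also assumes that no spacing rule appears in the material not available here.

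Label: cheap improvement.

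**What to change.** Treat this as a test condition and separate the two rules in STUDY DESIGN:

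- Keep the 9-hour interval for the fast.
- Require no interval-walking session or other strenuous exercise on the calendar day before each laboratory day, worded identically for Days 1, 2 and 3.
- Check compliance in the existing app log before Days 2 and 3. At Day 1, where there is no log, ask about exercise outside the programme.
- Record hours since last exercise at every visit, so that any remaining variation is visible in the analysis.

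Three sessions a week leave 7 − 3 = 4 days free, so the weekly programme can be completed around a visit. The cost is a sentence in the participant instructions, one recorded item per visit and an occasional rebooked visit.

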The application is a free personal trainer individualizing IWT by employing the on-board accelerometer and global positioning system (GPS) to specify walking intensity and speed. Intensities are determined, as with the accelerometer-based training device with the option of including GPS determined walking speed. Data from the fitness test is logged on a server, and as the CPR-number is a part of the profile information on the application, it will enable researchers and clinicians to combine it with health information using the Danish registers. However, the validity of the  $VO_{2peak}$  test functions and sensitivity to exercise adaptation of smart-phone based tests are at large, unknown. As the DD2 are establishing a large cohort consisting of ~50.000 newly diagnosed T2D patients, a valid tool for assessing exercise capacity on a large scale is needed [8]. Moreover, if valid, this application provides clinicians and researchers with an easy and cheap tool to estimate physical fitness in clinic and in very large samples and not only in T2D patients.

The  $VO_{2peak}$  test is conducted by the patients using their smart-phones and it is based on three self-selected walking paces - slow, moderate and high. It is uncertain to which extent the self-selected walking paces are adequate to reflect a  $VO_{2peak}$ . Furthermore, as T2D patients have limited experience with exercise training, we speculate that acclimatization to high intense walking and pacing during the  $VO_{2peak}$  test can improve the validity.

The aim of the study is to validate the ability of the smart-phone based IWT application to accurately reflect physical fitness in a sample of T2D patients. More specifically we aim to;

- 1) Develop an algorithm for conversion of the  $VO_{2peak}$  test output to energy expenditure and validate the algorithm against maximal oxygen consumption in an independent sample. We hypothesize that the  $VO_{2peak}$  test algorithm will be a valid measure of physical fitness if the peak test is performed at a sufficient walking pace.
- 2) Investigate the effect of acclimatization to high speed walking on the ability of the patient to perform a valid  $VO_{2peak}$  test. We hypothesize that acclimatization will increase walking economy in

the patients thus increase the walking pace during the  $VO_{2peak}$  test without any increase in physical fitness.

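### Walking economy is measured after a 75 g glucose load on Days 2 and 3 but not on Day 1, so any change from baseline is confounded with pre-test intake

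*Protocol*

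**What the plan says.** The Study design section states that "Table 1 describes the sequence of the tests included in the study", so the order within each column of Table 1 is the planned test order.

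- **Day 1:** medical examination, resting energy expenditure, anthropometry, two smart-phone tests, walking economy, graded maximal test. No glucose test is listed.
- **Day 2:** resting energy expenditure, 2-hour glucose test, DXA, two smart-phone tests, walking economy.
- **Day 3:** a repeat of Day 2, plus the graded maximal test.

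The same section sets the state on arrival: "Participants will be instructed to fast, refrain from smoking and physical activity for 9 hours prior to the tests". It then allows food before the walking tests: "After the assessment or REE or the OGTT the participants will be offered a meal". No content, amount or interval before walking is given. The Glucose Tolerance paragraph in METHODS says that "A standard 75 g oral glucose tolerance test (OGTT) will be performed over 2 hours".

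The Walking Economy paragraph defines the outcome by oxygen uptake: "The mean oxygen consumption of the later 2 minutes will be used". It keeps the treadmill speed the same on all test days and fixes nothing else between days. Aim 2 in BACKGROUND depends on this quantity: "We hypothesize that acclimatization will increase walking economy in" the patients, leading to a faster pace in the phone test with no gain in fitness.

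**The concern.** Oxygen uptake at a fixed speed measures economy only if the oxygen needed per unit of work is not altered by something else. Food alters it in two ways. Burning more carbohydrate yields more energy per litre of oxygen, so uptake falls for the same work. Processing a meal costs energy, so uptake rises. The protocol puts participants into a common fasting state on arrival, and then lets that state diverge between days before they walk.

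At stake is the interpretation of Aim 2. Training begins after Day 1, so Day 1 is the only economy measurement before acclimatization. If economy differs on Day 2 or Day 3, the change in intake could have produced, enlarged or hidden the difference.

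**Working it through.** The protocol gives no figure for an expected change in economy, its variability or a feeding effect, so there is no figure to reproduce. The check is a comparison of the days, followed by an illustration.

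**Step 1. Intake before walking economy, from Table 1 and the meal sentence**

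| Day | Glucose load | Meal |
|---|---|---|
| 1 | none listed | offered after resting calorimetry, undefined |
| 2 | 75 g | offered, undefined |
| 3 | 75 g | offered, undefined |

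The glucose test is described as following an overnight fast, so on Days 2 and 3 the meal must come after it.

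**Step 2. Which contrasts are affected**

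- Day 1 to Day 2: before to after the start of training, and no load to 75 g.
- Day 1 to Day 3: the same change in both.
- Day 2 to Day 3: matched on the glucose load. The optional meal can still vary, and this contrast contains no untrained measurement.

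**Step 3. Whether a comparison group could separate the effects**

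No. All participants train after Day 1. The randomisation in Additional Protocol 2 compares support with no support, and both arms train on the same test schedule.

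**Step 4. Illustration of the carbohydrate effect**

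Assumptions, none from the protocol: Weir's formula, energy per litre of oxygen = 3.941 + 1.106 × RER kcal, where RER is the respiratory exchange ratio; RER 0.85 on Day 1; and a range of higher values on Day 2. At equal energy cost:

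fall in oxygen uptake = 1 − (3.941 + 1.106 × RER1) / (3.941 + 1.106 × RER2)

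At RER 0.85 the denominator energy is 3.941 + 1.106 × 0.85 = 4.8811 kcal per litre.

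| RER on Day 2 | kcal per litre | Fall in oxygen uptake |
|---|---|---|
| 0.88 | 4.9143 | 1 − 4.8811/4.9143 = 0.68% |
| 0.90 | 4.9364 | 1 − 4.8811/4.9364 = 1.12% |
| 0.95 | 4.9917 | 1 − 4.8811/4.9917 = 2.22% |

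A fall in uptake reads as better economy, which is the hypothesised direction.

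**Step 5. The opposing effect**

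If the extra intake raises energy cost by a fraction t, the net ratio of uptakes is (1 + t) × 4.8811 / (energy at RER2). The two effects cancel when t = (energy at RER2)/4.8811 − 1, which is 0.68%, 1.13% and 2.27% in the three cases. A smaller t leaves an apparent improvement and a larger t an apparent deterioration. The documents give no basis for choosing t, so the net sign is open.

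**The case against.** The strongest reply has five parts.

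- **Day 1 is not a fasted day.** Participants are offered a meal then too, so the contrast is a meal against glucose plus a meal, and the shift may be small. This stands as to size. Because the meal is optional and undefined, nothing ensures that the days are matched.
- **The protocol names no Day 1 against Day 2 test of economy.** The Study design section uses the first two lab days for cross-validation, and STATISTICAL ANALYSES plans no test of economy. This stands: the contrast is inferred from the Aim 2 hypothesis. But Day 1 is the only measurement before training, so any contrast from an untrained state must start there.
- **A glucose test may also be given on Day 1.** The screening paragraph lists one among the examinations, Study design uses it to confirm diabetes status, and BIOLOGICAL MATERIAL plans about 100 mL of blood on each trial day. None of these places the test on Day 1, and Table 1 does not. If it is given then, Table 1 should say so.
- **Meal details may sit in laboratory procedures.** They may. A standard meal would still leave the glucose load unmatched unless it allows for it.
- **The illustrated shift is small and not compared with an expected acclimatization effect.** True. The protocol gives no such effect to compare it with.

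A reader might go further and turn the percentages in the working into a false-positive rate for Aim 2. The documents do not support that. It needs an exchange-ratio shift, a within-person variability and a significance test that the protocol does not give, and it would model only one of two opposing effects.

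A reader might also infer that the Day 1 and Day 3 results for Aim 3 are biased in the same way. The maximal test ends on a plateau with RER above 1.1, so the argument about fixed speed and equal energy cost does not carry over, and the phone estimate comes from accelerometer output. Intake does differ between those days, but no bias is shown.

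**Conclusion.** The concern holds for walking economy measured from Day 1. If the schedule is followed as written, every such change is confounded with intake before the test. With oxygen uptake as the only measure and no untrained group, later analysis of that measure cannot separate the two. This follows from Table 1 as printed and from the stated outcome definition.

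The size and net direction are unknown. The range of 0.7% to 2.2% is the carbohydrate part alone under assumed exchange ratios. The supported statement is that economy can shift without acclimatization, not that it will shift or in which direction. The point is worth correcting because it touches the mechanism proposed in one of three aims and the correction is cheap. It does not bear on the validation of the algorithm, which is the main purpose of the study.

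**What to change.** 1. Make intake and timing before the walking tests the same on all three days: a standard meal at a fixed interval before the first walking test, with the glucose from the tolerance test accounted for. An equal interval alone is not enough, because it leaves the glucose difference in place.
2. Report walking economy as energy cost calculated from oxygen uptake and carbon dioxide output alongside oxygen uptake, with RER by day. The gas-exchange data are already recorded. This removes the carbohydrate effect but not thermogenesis. If the two partly offset each other, energy cost alone could show the larger bias, so it supplements the matching in item 1 and does not replace it.
3. If intake cannot be matched, state in the protocol that economy changes from Day 1 to Day 2 or Day 3 cannot be attributed to acclimatization alone.

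The cost is less flexibility on the lab days and one extra derived variable.
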